**Figure 1 f1:**
[figure not shown]
Flow chart of patient recruitment and study implementation.

The study used a simple randomization method. The steps are as follows: first, in Excel, we used the RAND function to generate a number between 0 and 1. The function is invoked by entering “=RAND()” in any cell and pressing Enter. The generated number determines the group assignment for each patient: if the number is from 0 to 0.5 (excluding 0.5), the patient is assigned to the intervention group; if it is from 0.5 to 1 (excluding 0.5), the patient is assigned to the control group. If the number is exactly 0.5, the process is repeated until a valid random number is obtained.

The blinded method used in this study involves several categories of individuals:

Medical staff in the research department (blinded): responsible for patient recruitment, informing patients of admission and follow-up times and locations, and conducting basic biochemical and imaging examinations for admission and follow-up, they are unaware of patient group assignments.Investigators (blind): Their responsibilities are strictly limited to one-on-one data collection with patients; they do not participate in other research activities to ensure data specificity and accuracy. Investigators are unaware of patient group assignments.Data processing personnel (blind): They receive coded data (Group A/Group B) and are unaware of the specific assignment relationship between Groups A/B and the intervention or control groups.Patients (unblinded): The intervention group is guided by the researcher to follow the Artificial Intelligence-Empowered Mobile Health Official Account and instructed on its use. The control group does not receive this service.System administrator (unblinded): Responsible for online management and answering questions for patients in the intervention group; their service is limited to patients in the intervention group, as only this group receives the Artificial Intelligence-Empowered Mobile Health intervention.

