#### Control group: standard care

2.5.1

The control group was not completely blank. At the time of enrolment, patients in the control group received standard oral health education, including explanations of the surgical procedure and precautions, routine preoperative examinations, and guidance on postoperative precautions. Any questions or concerns raised by patients were answered in detail.

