#### Intervention group: standard care + artificial intelligence-empowered mobile health

2.5.2

Based on the physiological recovery cycle after abortion and the critical time window for screening complications, this study was designed as a two-week continuous intervention. The intervention protocol was developed by a multidisciplinary team comprising public health experts, clinician doctors, nurses, psychologists, and statistical analysts, integrating expertise from all relevant fields. The core intervention method employs Artificial Intelligence-Empowered Mobile Health, guided by Swanson’s Theory of Caring as a theoretical framework. The two-week intervention period is divided into distinct phases, each of which is strictly implemented by the fundamental care dimensions of this theory.

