**Specific Methods:**

On the day of the follow-up examination, the doctor will provide face-to-face guidance on key points for long-term post-operative care.Patients will be instructed that they can consult on authoritative social media platforms if they encounter any issues.

**Swanson’s Theory of Caring:** Being with, Maintaining belief.

**Intervention providers:** Researcher.

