**Intervention content:**

Researchers provide accompaniment and guidance to patients during follow-up appointments.

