**Specific Methods:**

Contact the patient proactively before the follow-up examination to reconfirm the time, location, and examination items.Accompany the patient throughout the follow-up examination on the day of the appointment, explaining the environment and the purpose of each examination to alleviate any feelings of unfamiliarity.Pay attention to the patient’s emotions, provide patient companionship and positive support, and encourage them to face the future with optimism.

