The Posttraumatic Stress Disorder (PTSD) Checklist for DSM-5 (PCL-5) is used to measure symptoms that meet the criteria of the DSM-5. The scale consists of four dimensions: intrusive symptoms, avoidance, cognitive/emotional negative changes, and hyperarousal, with a total of 20 items. Each item is scored on a scale of 0 to 4 (0 = “not at all” to 4 = “extremely “). The total score range is 0–80 points, with higher scores indicating more severe PTSD symptoms and greater functional impairment. The overall Cronbach’s alpha for the original scale was 0.94 (41).

Quality of life is measured using the EuroQol Visual Analogue Scale (EQ-VAS), which is used to assess the overall health status of participants. The EQ-VAS is a vertical scale on which respondents record their self-rated health status (42). The scale ranges from 0 to 100, with 0 representing “the worst health state you can imagine” and 100 representing “the best health state you can imagine”.

Physiological and biochemical data: Professional medical staff at the Inner Mongolia Maternity and Child Health Care Hospital, who are qualified to perform such procedures, strictly adhere to clinical operating procedures and hospital testing standards to conduct human chorionic gonadotropin (HCG) level measurements and ultrasound examinations on patients. The HCG level measurement employs chemiluminescence immunoassay, utilizing the advanced, fully automated chemiluminescence immunoassay analyzer to precisely quantify the level of human chorionic gonadotropin in serum. Ultrasound examinations are conducted using a color Doppler ultrasound diagnostic instrument, with experienced ultrasound specialists conducting detailed examinations and assessments of uterine morphology, endometrial thickness, and the presence of any residual material within the uterine cavity.

Qualitative interview: Researchers initially developed a semi-structured interview outline based on the research objectives and a review of relevant literature. After consulting with qualitative research experts and conducting preliminary interviews, the research team revised the interview outline based on expert discussions and finalized the content of the interview outline. During the interviews, researchers needed to maintain a certain degree of openness and flexibility. The outline included, but was not limited to, the following questions:

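### The researcher's escort through the follow-up examination, listed only for the intervention arm, may reveal the arm to ultrasound staff whom the protocol declares blind

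*Protocol article*

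**What the plan says.** **Declared blinding (section 2.1).** The medical staff who recruit patients and examine them are listed as blind. Their tasks include "conducting basic biochemical and imaging examinations for admission and follow-up, they are unaware of patient group assignments".

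**Escort (section 2.5.4, Phase 3, the step headed Being with and Maintaining belief).** The provider line reads "Intervention providers: Researcher". The intervention content is "Researchers provide accompaniment and guidance to patients during follow-up appointments", and the methods add: "Accompany the patient throughout the follow-up examination on the day of the appointment, explaining the environment and the purpose of each examination".

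**Arm to which this belongs.** Section 2.5.2, on the intervention group, introduces the phased programme: "The two-week intervention period is divided into distinct phases, each of which is strictly implemented by the fundamental care dimensions of this theory". Section 2.5.4 then sets out those phases.

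**Control care (section 2.5.1).** "At the time of enrolment, patients in the control group received standard oral health education". The section goes on to the routine preoperative tests, advice for after the operation and answers to questions. It mentions no escort at follow-up.

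**Attending doctor (section 2.5.4, Phase 3, the step headed Knowing).** The physical and auxiliary examinations are themselves listed as intervention content, with the attending doctor and the researcher as providers.

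**Outcome (section 2.6.2.1 and Table 1).** Ultrasound and HCG are secondary outcomes, ticked at T1 only. The ultrasound covers "assessments of uterine morphology, endometrial thickness, and the presence of any residual material within the uterine cavity", judged by ultrasound specialists.

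**The concern.** A blinding statement is only as good as the procedures around it. Here the follow-up visit is both the last contact of the intervention and the occasion on which the ultrasound outcome is assessed. If the researcher stays beside intervention women during their examinations and nothing similar is planned for controls, the companion's presence can tell the imaging staff which arm the woman is in.

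What is at stake is how far a difference between arms in the ultrasound findings can be trusted. Whether residual material is present depends on the reader's judgement, and endometrial thickness depends to some degree on how the measurement is taken. If the reader may know the arm, a difference could come partly from the reading. A trial report that repeats section 2.1 would also claim assessor blinding that the trial's own intervention procedures put in doubt.

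The ultrasound is where blinding of these staff has most to protect. The psychological scales are completed by women who know their arm, and HCG is quantified by machine.

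**Working it through.** The plan gives no figure on this point, so the check sets the sections side by side.

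1. **Is the escort specific to one arm?** It stands under an intervention-content heading in section 2.5.4, which carries out the programme that section 2.5.2 assigns to the intervention group. Section 2.5.1 lists nothing comparable. The natural reading is that the escort is arm-specific. This is inferred from the structure; no sentence says that controls come unaccompanied.

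2. **Does the escort cover the scan?** The wording runs through the whole follow-up examination and has the researcher explain the purpose of each test. The ultrasound is one of the T1 tests in Table 1. Nothing places the researcher outside the scan room, and nothing says explicitly that the researcher goes in.

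3. **Are the scanning staff among those declared blind?** Yes. Section 2.1 names imaging at follow-up.

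4. **Is there a safeguard that would keep the arm hidden anyway?** None is described. The article mentions no reading of stored images by someone without patient contact and no matching escort for controls.

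5. **Is there a second route?** Yes. The attending doctor is a Phase 3 provider in the step that contains the examinations. In Phase 2, the researcher summarises feedback from the women's exchanges with the AI for that doctor each day, so the doctor can know who is in the intervention arm. The article does not say that the attending doctor performs the ultrasound; section 2.6.2.1 gives it to ultrasound specialists. Nor does it keep the examination step separate from the people who deliver the intervention.

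6. **Which outcomes are exposed?**

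| Outcome | How obtained | Exposed to this route? |
|---|---|---|
| Ultrasound: morphology, endometrial thickness, residual material | Specialist's assessment at T1 | Yes |
| HCG | Automated chemiluminescence analyser | Little |
| PHQ-9 (primary) | Self-rated by women who know their arm | No |
| Other psychological scales and EQ-VAS | Self-rated by women who know their arm | No |

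So sections 2.1 and 2.5.4 are in conflict over the imaging staff, and the consequence falls on the ultrasound items.

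**The case against.** Several points can fairly be made on the other side.

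- **Controls may also have company.** Section 2.5.1 describes control care around enrolment and is silent on T1. Sections 2.1 and 2.9 have investigators meet participants one-on-one for data collection without limiting this to one arm, and section 2.8 speaks of researchers giving guidance during the whole study. A reader might infer that a woman who arrives with a companion is visibly in the intervention arm and one who arrives alone is a control. The documents do not go that far. The cue works only if the imaging staff recognise the companion as the intervention researcher and know that one arm alone is escorted, and neither is stated. This stands, and it is why the point is that the arm may be revealed.

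- **The blinding may survive in practice.** A reader might infer that the imaging outcome is simply not blinded. The text supports a risk and a conflict between sections, not an established unblinding.

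- **The bias has no known size.** A reader might want a false-positive rate. Take a two-sample t-test at the two-sided 5% level, 50 women per arm and no true effect. An assumed shift in reading of 0.1 SD gives about 8%, and one of 0.4 SD about 51%. The result is set almost wholly by the assumed shift, for which the documents give no basis. It also assumes full follow-up, although section 2.3 raises the sample to 50 per group to allow for loss, and it does not fit a present-or-absent finding such as residual material. These rates are no estimate for this trial.

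- **The outcome is secondary.** True. The primary outcome is untouched, and this limits the weight of the point.

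That a journal article condenses the full protocol does not answer the point, because both sides of the conflict are printed in the article.

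**Conclusion.** The point holds in limited form. Section 2.1 declares the follow-up imaging staff blind. Section 2.5.4 makes the researcher's company during the follow-up examination part of the intervention, with no counterpart listed for controls, and names the attending doctor as a provider in the step that contains the examinations. The arm may therefore be revealed to those who assess the T1 ultrasound.

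The conclusion rests on two readings: that the escort is arm-specific, from the section structure, and that it extends to the scan, from the breadth of the wording. Both are natural, but neither is stated outright. The effect is confined to the ultrasound items, and its size cannot be derived from the documents. The sections should be reconciled; the primary analysis does not depend on it.

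**What to change.** Reconcile section 2.1 with Phase 3 of section 2.5.4 in one of two ways.

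**Option A: protect the blinding.**
- Keep the researcher out of the imaging staff's sight until the scan is recorded. Stopping at the door in their view would not be enough.
- Send the scan request with the study number only.
- Ask women in both arms not to mention the service during the examination.
- State that the scan is done by staff who deliver no component of the intervention. This closes the route through the attending doctor, which moving the escort alone would leave open.

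**Option B: correct the statement.** Delete the blinding claim for imaging staff in section 2.1 and report the ultrasound outcome as open-label.

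Option A needs a sentence in Phase 3 and a few lines in the T1 procedure. Its small downside is that the woman is without the escort during the scan. Option B is a change of wording only, at the price of a less secure ultrasound comparison.

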### Outcomes

2.6

#### Primary outcome

2.6.1

##### Depression levels

2.6.1.1

In this study, symptoms of depression were assessed using PHQ-9. This scale consists of nine items, each corresponding to the core symptoms of depression in the Diagnostic and Statistical Manual of Mental Disorders (DSM), such as depressed mood, sleep problems, and fatigue (30). Each item is scored on a scale of 0–3 points(0 = “not at all” to 3 = “nearly every day”). The scores for the 9 items are added together, with a total score ranging from 0–27 points. The higher the total score, the more severe the depressive symptoms. The severity of depression is classified according to the total score as follows: 0–4 minimal depression, 5–9 mild depression, 10–14 moderate depression, 15–19 moderate depression, 20–27 severe depression. The Cronbach’s alpha for the Chinese version of the PHQ-9 is 0.86 (32).

#### Secondary outcomes

2.6.2

##### Psychological and behavioral health

2.6.2.1

Anxiety symptoms are measured using the three-item short form of Generalized Anxiety Disorder (GAD-3). Each item is scored on a scale of 0–3 points(0 = “not at all” to 3 = “nearly every day”). The scores for the three items are added together, with a total score range of 0–9 points. With higher scores indicating greater anxiety levels, the RiskSLIM algorithm assigns different weights to each item to form a weighted total score. The optimal practical cutoff value for GAD-3 is 15 (33). The Cronbach’s α for this scale among nursing students was 0.934 (34).

Stress levels were measured using the Perceived Stress Scale-4 (PSS-4). It consists of four items, and each item is scored on a scale of 0–4 points(0 = “never” to 4 = “very often”), including two reverse-scored items. The total score ranges from 0 to 16 points, with higher scores indicating more significant psychological stress in patients (35, 36). The Chinese version of the PSS-4 demonstrated a Cronbach’s alpha of 0.473 when validated among a large community-based general population. In a study examining the relationship between perceived stress and marital satisfaction among infertile couples, the Cronbach’s alpha coefficient for the PSS-4 was 0.572 (37).

Social support is measured using the Perceived Social Support Scale Short Form (PSSS-SF). This scale consists of three items designed to assess an individual’s self-perceived levels of social support. Each item is scored on a scale of 1 to 7 points (1 = “not at all compatible” to 7 = “fully compatible”). The total score range for this scale is 3 to 21, with higher scores indicating higher levels of perceived social support (38).

The Body Image–Acceptance and Action Questionnaire–5 (BI-AAQ-5) is used to measure body image flexibility. The scale consists of 5 items. Each item is scored on a scale of 1 to 5 (1 = “not at all compatible” to 5 = “fully compatible”). Some items require reverse scoring. The total score range for the scale is 5 to 25 points. Higher scores indicate greater acceptance of body image and fewer avoidance behaviors toward negative body experiences. The overall Cronbach’s alpha for the scale during development was 0.85 (39, 40).

The Posttraumatic Stress Disorder (PTSD) Checklist for DSM-5 (PCL-5) is used to measure symptoms that meet the criteria of the DSM-5. The scale consists of four dimensions: intrusive symptoms, avoidance, cognitive/emotional negative changes, and hyperarousal, with a total of 20 items. Each item is scored on a scale of 0 to 4 (0 = “not at all” to 4 = “extremely “). The total score range is 0–80 points, with higher scores indicating more severe PTSD symptoms and greater functional impairment. The overall Cronbach’s alpha for the original scale was 0.94 (41).

Quality of life is measured using the EuroQol Visual Analogue Scale (EQ-VAS), which is used to assess the overall health status of participants. The EQ-VAS is a vertical scale on which respondents record their self-rated health status (42). The scale ranges from 0 to 100, with 0 representing “the worst health state you can imagine” and 100 representing “the best health state you can imagine”.

Physiological and biochemical data: Professional medical staff at the Inner Mongolia Maternity and Child Health Care Hospital, who are qualified to perform such procedures, strictly adhere to clinical operating procedures and hospital testing standards to conduct human chorionic gonadotropin (HCG) level measurements and ultrasound examinations on patients. The HCG level measurement employs chemiluminescence immunoassay, utilizing the advanced, fully automated chemiluminescence immunoassay analyzer to precisely quantify the level of human chorionic gonadotropin in serum. Ultrasound examinations are conducted using a color Doppler ultrasound diagnostic instrument, with experienced ultrasound specialists conducting detailed examinations and assessments of uterine morphology, endometrial thickness, and the presence of any residual material within the uterine cavity.

Qualitative interview: Researchers initially developed a semi-structured interview outline based on the research objectives and a review of relevant literature. After consulting with qualitative research experts and conducting preliminary interviews, the research team revised the interview outline based on expert discussions and finalized the content of the interview outline. During the interviews, researchers needed to maintain a certain degree of openness and flexibility. The outline included, but was not limited to, the following questions:

What specific functionalities of Artificial Intelligence-Empowered Mobile Health did you use?Which Artificial Intelligence-Empowered Mobile Health functionalities had a positive effect on your health, and which ones had no effect or even had a negative effect?How did using Artificial Intelligence-Empowered Mobile Health affect your mental health? What do you think caused these effects?With the help of Artificial Intelligence-Empowered Mobile Health, what did you learn about post-abortion care?To what extent did you trust the health information provided by Artificial Intelligence-Empowered Mobile Health? Did you find its responses reliable? Why?’How did you feel when Artificial Intelligence-Empowered Mobile Health attempted to comfort or encourage you? Do you perceive this emotional support as genuine? Please elaborate on your feelings.”What were your expectations of Artificial Intelligence-Empowered Mobile Health prior to using it? How did its actual performance differ from your expectations?’Compared to support provided by healthcare professionals or family/friends, what unique aspects did you find in interacting with Artificial Intelligence-Empowered Mobile Health? Which form of support do you prefer? Why?’

Patient demographic information will be collected through the case system and self-designed questionnaires. (**Table 1**).

**Table 1 T1:** Variables and measures collected at every time point.

Variables	Date source	Measures	Baseline(T0)	Post-intervention(T1)
Intervention preparation	/	Eligibility screen, Informed consent and Allocation	✓	
Covariates	Baseline questionnaire	Sociodemographic information	✓	
	Baseline questionnaire and Follow-up questionnaire	Behavioral information	✓	✓
Primary outcome	Baseline questionnaire and Follow-up questionnaire	Patient Health Questionnaire-9 (PHQ-9)	✓	✓
Secondary outcome	Baseline questionnaire and Follow-up questionnaire	Generalized Anxiety Disorder-3, GAD-3	✓	✓
		Perceived Stress Scale 4, PSS-4	✓	✓
		Perceived Social Support Scale Short Form, PSSS-SF	✓	✓
		Body Image-Acceptance and Action Questionnaire-5, BI-AAQ-5	✓	✓
		Posttraumatic Stress Disorder Checklist for DSM-5, PCL-5	✓	✓
		EuroQol Visual Analogue Scale, EQ-VAS	✓	✓
	Clinical examination and laboratory tests	Ultrasound, human chorionic gonadotrophin, HCG		✓
Qualitative results	semi-structured interviews	Effect of the trial		✓

### Statistical analysis

2.7

After the trial is completed, all collected case data and questionnaire responses will be organized and summarized. Data storage will be managed using Microsoft Office 2017, while statistical analysis will be conducted using SPSS Statistics 27.0 software. Count data will be presented as case numbers (N) and percentages (%). The normality of continuous data will be assessed; normally distributed data will be presented as mean ± standard deviation, while non-normally distributed data will be presented as median (interquartile range) and interquartile range (P25-P75). Appropriate statistical tests (e.g., independent samples t-test, Mann-Whitney U test, and chi-square test) will be used to compare baseline characteristics between the intervention and control groups based on data type. Longitudinal analysis of follow-up data will be conducted using generalized estimating equations (GEE) to compare differences in outcomes between the two groups. Two-sided tests will be used, with statistical significance set at p < 0.05. In cases of missing data, multiple imputation techniques will be applied, considering the randomness of missing data. Multiple imputation involves generating multiple complete datasets by replacing missing values with reasonable estimates derived from observed data and imputation models. Compared to single imputation methods, this approach preserves the variability of the dataset and enhances the reliability of results. Multiple imputation will be performed using established statistical software (e.g., SPSS or R). Sensitivity analysis will also be conducted to assess the robustness of results under various assumptions regarding missing data. This comprehensive approach ensures the validity and reliability of research findings while maintaining statistical integrity throughout the analysis process and accounting for missing data. Qualitative interview audio files will be transcribed verbatim and anonymized, and analyzed using Grounded Theory with NVivo (Version 12, QRS International, Doncaster, Australia). Qualitative and quantitative data will be incorporated to better interpret the results across multiple stages during the trial.

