**Methods:**

This study is a mixed-methods research protocol to be implemented at the Inner Mongolia Maternity and Child Health Care Hospital. A total of 100 women after abortion will be included and randomly assigned to either the intervention group or the standard care group. The intervention group will receive two weeks of Artificial Intelligence-Empowered Mobile Health intervention guided by Swanson’s Theory of Caring, including medical knowledge about abortion, post-operative diet, and exercise guidance. The standard care group will receive standard prenatal care. The primary outcome is the change in depression levels, while secondary outcomes include anxiety, perceived stress, perceived social support, and other factors. This study uses IBM SPSS Statistics 27.0 and NVivo 12.0 for data analysis, employing descriptive statistics, normality tests, Mann–Whitney U, Wilcoxon, and chi-square tests.

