### Sample size

2.3

This study is a mixed-methods research. The intervention group will receive Artificial Intelligence-Empowered Mobile Health interventions, while the control group will receive standard care. Based on previous research findings, nursing interventions based on Swanson’s Theory of Caring have been shown to significantly reduce depression and anxiety levels in women who have experienced abortion, and can serve as a reference for effect size (29). The Minimum Clinically Important Difference (MCID) was selected as a reduction of ≥5 points on the Patient Health Questionnaire-9 (PHQ-9), which is considered clinically meaningful (30). The standard deviation (SD) is based on previous studies showing that the SD of PHQ-9 in the abortion population is approximately 6–8 points. The test level α = 0.05 and test efficacy 1-β = 0.90 are set, and according to the randomized controlled trial mean comparison formula:

$$n=\frac{{\left(Z_{\alpha /2}+Z_{\beta }\right)}^{2}\cdot 2\sigma^{2}}{\Delta^{2}}$$

The sample sizes for each experimental group are equal. Z_α/2_ = 1.96, Z_β_ = 1.28, σ = 8, Δ = 5 in this example. The sample size for each group can be calculated as n = 42 people. Considering the follow-up missing rate, the sample size for each group is increased to 50 people, for a total of 100 people.

Qualitative research is guided by the principle of information saturation, meaning that interviews with patients are stopped once a certain number of participants have been reached and no new information is emerging. Therefore, this study does not specify a minimum sample size for qualitative research.

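### The abstract and section 2.7 name different analysis methods, no single primary PHQ-9 analysis is fixed, and adjustment for baseline PHQ-9 is not specified

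*Protocol article*

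**What the plan says.** The abstract defines the primary endpoint as a change: "The primary outcome is the change in depression levels". It describes the analysis of the whole study as "employing descriptive statistics, normality tests, Mann–Whitney U, Wilcoxon, and chi-square tests". GEE is not in that list, and no method in it is tied to an outcome.

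Section 2.7 differs. The t-test, Mann–Whitney U and chi-square test "will be used to compare baseline characteristics between the intervention and control groups based on data type". For outcomes it says: "Longitudinal analysis of follow-up data will be conducted using generalized estimating equations (GEE) to compare differences in outcomes between the two groups". Wilcoxon does not appear. No model terms are given, so adjustment for baseline PHQ-9 is neither stated nor ruled out. On the error rate it says: "Two-sided tests will be used, with statistical significance set at p < 0.05".

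Section 2.3 sizes the trial with the formula for comparing two means ("The test level α = 0.05 and test efficacy 1-β = 0.90 are set"), using an SD of 8 and a difference of 5 points, and states 42 per group before allowance for loss to follow-up. Section 2.1 and Table 1 place the PHQ-9 at baseline and two weeks only. Table 1 also has a covariates block that includes "Behavioral information" at both time points.

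**The concern.** A reader of the abstract would expect rank tests; a reader of section 2.7 would expect GEE. Neither can tell which single number will be the trial's primary result. With the GEE terms open, several analyses of the same PHQ-9 data would fit the text, and they differ in precision. What is at stake is a choice of analysis left open until after the data are seen, and power forgone although the variable that would supply it, baseline PHQ-9, is scheduled for everyone.

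The abstract also names Wilcoxon beside Mann–Whitney U, which suggests the paired signed-rank test. A paired test within an arm does not compare the randomised arms, so it could only be descriptive.

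**Working it through.** **Inputs.** From section 2.3: SD σ = 8, difference Δ = 5, 42 per group, α = 0.05, power 0.90. From section 2.7: two-sided tests. From section 2.1 and Table 1: two time points. Assumed, because the article gives no value: the T0–T1 correlation ρ, shown at 0.3, 0.5 and 0.7, and the same SD at T0 and T1.

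**The plan's own figure.** Section 2.3's formula with its own inputs gives (1.96 + 1.28)² × 2 × 8² / 5² = 53.7, so 54 per group, not 42. That is a separate matter. The number 42 is kept below as the plan's own evaluable number.

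**What the GEE would estimate.** With T0 and T1 complete, a GEE with group, time and group-by-time terms has as its interaction the difference between arms in mean change. A check on one simulated data set of 42 per arm gave an estimate of −5.708 and a standard error of 1.669 both ways.

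**Effective SDs.**
- T1 score only: σ = 8.
- Change or group-by-time: σ√(2(1 − ρ)).
- T1 adjusted for baseline (ANCOVA): σ√(1 − ρ²).

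The variance ratio of change to ANCOVA is 2(1 − ρ)/(1 − ρ²) = 2/(1 + ρ), which exceeds 1 for every ρ below 1.

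**Power.** The standard error is SD × √(2/42). Power comes from the two-sided t-test; the one degree of freedom spent on the covariate is ignored.

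| ρ | SD change | SD ANCOVA | Variance ratio | Power, T1 only | Power, change | Power, ANCOVA |
|---|---|---|---|---|---|---|
| 0.3 | 9.47 | 7.63 | 1.54 | 80.8% | 66.7% | 84.3% |
| 0.5 | 8.00 | 6.93 | 1.33 | 80.8% | 80.8% | 90.5% |
| 0.7 | 6.20 | 5.71 | 1.18 | 80.8% | 95.5% | 97.7% |

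The normal approximation agrees within about one point: for change and ANCOVA, 67.7% and 85.1%, 81.7% and 91.1%, 95.9% and 98.0%. Against a T1-only comparison, the change analysis loses power only for ρ below 0.5. Against ANCOVA it loses at every ρ below 1, though by little when ρ is high.

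**The case against.** The strongest defence is that the abstract's list covers the whole study and calls nothing primary. Section 2.7 gives Mann–Whitney and chi-square a place in the baseline comparison, and GEE is the only outcome method it names. GEE terms are commonly left to an analysis plan, which is not shown here. A change or group-by-time analysis is a valid randomised comparison and fits an endpoint worded as a change. All of this stands. It narrows the point but does not remove the mismatch: the abstract omits the only outcome method in section 2.7 and names a test that has no role there.

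A reader might infer more than the article supports:

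- **That the plan is unadjusted for baseline.** The article is silent; it does not say so.
- **That a normality test decides the outcome test.** In section 2.7 normality governs how data are presented, and data type governs the baseline tests.
- **That one-arm-only significance on Wilcoxon would be read as an effect.** The article does not say that Wilcoxon is run within arms, applied to the PHQ-9 or interpreted that way. Simulated rates for that practice also rest on assumptions. With no true difference and ρ = 0.5, exactly one arm is significant in about 8% of trials if neither arm improves, and in 46–47% if both improve by 2–3 points.
- **That the GEE would average T0 and T1 into one group effect.** Nothing in section 2.7 says so.
- **That T1 behaviour will be adjusted for.** Table 1 is a collection schedule. It does not define behavioural information or put it into a model.

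**Conclusion.** The point holds in a limited form and should be fixed. Two current statements of the analysis do not match, and no single primary PHQ-9 analysis is fixed. If the unspecified GEE turns out to be the usual group-by-time model, the cost relative to baseline adjustment is about 18 percentage points of power at ρ = 0.3, 10 at ρ = 0.5 and 2 at ρ = 0.7. These sizes rest on the plan's SD of 8, difference of 5 and 42 evaluable per arm, on equal SDs at T0 and T1, and on an assumed ρ. The loss is one of efficiency, not validity. The documents do not support a charge that the plan commits to an invalid or unadjusted primary analysis.

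**What to change.** 1. In section 2.7, name one primary analysis: linear regression of T1 PHQ-9 on arm and baseline PHQ-9 (ANCOVA), reported as an adjusted mean difference with 95% CI. If GEE is to be kept, a GEE with the two arms' baseline means constrained equal does the same job. The endpoint can still be described as change, because with baseline in the model the arm coefficient is the same whether T1 or T1 minus T0 is the response.
2. Use the same model for the other scales measured at both T0 and T1.
3. Rewrite the abstract's list to match section 2.7. Remove Wilcoxon, or state that any within-arm test is descriptive.
4. If covariates from Table 1 enter the model, say which, and use their T0 values only.

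The cost is wording. No new data, visits or participants are needed, but the change should be made and dated before outcome data are seen.
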